**The transdiagnostic, group psychological treatment of the experimental group.**

The psychological intervention offered (which will be applied by psychologists) will be protocolised (with a Therapist's Manual) and described in a document addressed to the patient. The patients assigned to the experimental group will receive 7 sessions of 1.5 hours duration in groups of approximately 10 people, spread over 24 weeks, with a greater temporal frequency at the beginning of the treatment (one session per week) and a progressive extension of the time interval between sessions as the treatment progresses. The treatment protocol will be adjusted to the following contents:

Sessions 1: This group will start the psychological treatment with psychoeducational training, in order to provide participants with concrete information (oral and written), as well as information resources (e.g., books, website), on stress, emotions, anxiety, anger, depression, the role of cognitive processes and biases on emotion, emotional learning, emotion regulation, relationships between emotion and behaviour, etc., trying to adapt the contents to the needs of the participants. In all sessions, patients will be motivated to take an active role in the treatment and to carry out the corresponding daily homework.

Session 2: Relaxation techniques will be introduced, with a mixture of Bernstein and Borkovec's progressive muscle relaxation training, abdominal breathing and imagery training. The principles of these exercises, the intended objectives and how to perform the training will be explained. In addition, patients will be asked to practice these exercises daily at home with an audio recording that will be provided, lasting approximately 30 minutes. In order to develop motivation and the habit of practising this task, patients will be asked to make a graphic self-recording of their daily evaluation of the degree of relaxation experienced after the practice, throughout the 24 weeks of the intervention.

Sessions 3-4: These sessions will be devoted to practice in cognitive restructuring and emotional self-regulation training. [66, 67] First, they will be instructed, in a general way, on what emotions are, how they manifest (i.e., at a cognitive-subjective, physiological and behavioural level) anxiety, fear or sadness; as well as in which situations these responses occur, which reactions help to improve adaptation to the environment or which do not, and which strategies are appropriate and which are not to regulate these reactions. It will also be explained how some emotional disorders can easily develop (e.g., when stress increases, uncontrolled anxiety reactions are triggered, too much importance is given to a physiological response that has no voluntary control and attention is focused on the physical sensations it produces). By means of case presentations, it will be shown how it is possible to detect and change distorted thoughts, irrational beliefs, threatening appraisals [68], cognitive biases [52], emotion regulation strategies, etc., which are associated with intense negative emotional states of anxiety, anger or other negative emotions in everyday life. Afterwards, we will work with concrete samples of emotional events experienced by patients in the last week and show them how they should approach these events from a new cognitive-emotional perspective that will help them better understand their errors and biases in emotion regulation, and how they can restore emotional self-regulation through changes in information processing (e.g., encouraging neutral information processing), encouraging neutral or positive information processing, using distraction, reducing the importance and magnification of the threat or loss, reducing ruminative processes, worry and biases of attention focused on the threat or loss, increasing positive self-instructions and perceived self-efficacy, etc.).

Sessions 5-6: These will focus on behavioural techniques and will be aimed at patients learning or relearning and regaining self-management of situations, emotions and behaviours that they had failed to manage correctly in their daily lives. [66,67] This intervention should include a treatment package composed of several psychological techniques (e.g., exposure) that are initiated in the group sessions and should be practised daily at home (in addition to relaxation and self-help book): self-observation, stimulus control, reinforced behavioural training, exposure without safety behaviours, coping skills training, etc. Group sessions will review recently experienced emotional events, reinforce successes, correct errors and continue to encourage decreasing cognitive biases (e.g., attention, interpretation, memory, attribution) that trigger emotional reactions that alter behaviour by providing more homework assignments that involve rehearsal, practice, reinforcement, correction, progressive exposure, etc.

Session 7: This will include relapse prevention, pointing out that relapses do not mean a return to the beginning, a total loss of therapeutic gains, nor a failure, but a new challenge to be overcome and an opportunity to learn more and consolidate what has been learned. To this end, any relapses that may have occurred should be analysed, indicating how to proceed to overcome the difficulties and learn from such setbacks. The session will be completed with a general review of all that has been learned and a generalisation to similar problems that may arise in the future, always emphasising that in order to overcome these difficulties, technical tools are now available, as well as new coping skills (which continue to be developed through practice with these techniques), which have proved useful in overcoming the problems that have already been solved. It will be recommended that these skills be used to cope with future life stress and not the old habits that led to the development of their emotional problems.

**Treatment using relaxation techniques**

The treatment using Bernstein and Borkovec's progressive muscle relaxation technique will be applied by psychologists. Patients assigned to the control group, as in the experimental group, will receive 7 sessions of 1.5 hours duration in groups of approximately 10 people, spread over 24 weeks, with a greater temporal frequency at the beginning of the treatment (one session per week) and a progressive extension of the time interval between sessions as the treatment progresses.

Both groups, experimental and control, together with the treatments described above, will follow the usual treatment by their GP, according to their usual procedure, typically pharmacological treatment and unstructured support. The number of consultations received during the period of participation in the study will be taken into account.

**Statistical analysis**

Both parallel groups will be tested for equivalence on pre-treatment measures. In the efficacy analysis, 2x2 (group x treatment) intergroup-intragroup ANOVAs will be carried out on the dependent measures: 1) symptoms of anxiety, depression and somatisation; 2) cognitive-emotional factors associated with symptoms; 3) occupational, family and social dysfunction; 4) quality of life; 5) satisfaction with care received; 6) cost-effectiveness analysis (e.g., frequentation, drug consumption). The effect size of both groups on the different dependent variables will be calculated, as well as their precision (95% confidence intervals), taking into account the number of sessions received. The percentages of patients in both groups who have decreased their clinical symptom scores by 50% and by one standard deviation, as well as the percentages of probable cases with mental disorders (anxiety, depressive and somatoform) before and after treatment, according to the cut-off points and decision rules for diagnosis, will also be calculated. The primary analyses will follow the "intention-to-treat" principle, so that all individuals who have entered the study will be considered in their corresponding group, even if they have not complied with their protocol. This will allow the objective of randomisation to be maintained until the end of the study, i.e. to reduce the likelihood of biasing the results.

The cost-effectiveness analysis will be carried out by calculating the increase in cost-effectiveness ratios, defined as the difference between the mean costs divided by the increase in effectiveness between the different therapeutic alternatives compared (ICER).

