**Abstract:**

The aim of this study is to test the cost-effectiveness and cost-utility of adding a transdiagnostic group cognitive-behavioural therapy (TD-CBT) to treatment as usual (TAU) for emotional disorders in primary care . A single-blind randomized controlled clinical trial will be conducted to compare the TD-CBT group therapy plus TAU to progressive muscle relaxation (PMR) group plus TAU in individuals, aged 18 to 65, with emotional disorders in four primary care centres located in Cantabria, Spain. The study will take a societal perspective. Psychological assessments will be carried out at baseline, post-treatment, and 12-months follow-up. The assessments will include measures of clinical symptoms (anxiety, depression, and/or somatic), dysfunction, cognitive-emotional factors (ruminative processes, pathological concern, attentional and interpretative biases, emotion regulation strategies and meta-cognitive beliefs), and satisfaction with the treatment received. Data on health service use, including medication and days of absence from work, will be collected from electronic medical records. The primary outcomes are the incremental cost-effectiveness ratios (ICER) based on the difference in mean costs and effectiveness between interventions and incremental cost-utility ratios (ICURs) based on health-related quality of life at post-treatment and 12-month follow-up. Secondary outcome measures include clinical symptoms, quality of life, functioning and treatment satisfaction. Bootstrap sampling will be used to assess the uncertainty of the results. Secondary moderation and mediation analyses will also be conducted. In addition, in sessions' number 1, 4 and 7 of both treatment arms, two questionnaires will be administered that collect therapeutic alliance and group satisfaction. The main study hypothesis is that adding TD-CBT to TAU in primary care will be more cost-effective than TAU plus PMR. In addition, these gains will be maintained in the 12-month follow-up. If it is successful, the dissemination of cost-effective treatment can help to overcome problems in accessing psychological treatment for emotional disorders in the context of an increasing demand for mental healthcare in primary care.

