**Outcome Measures**

Primary Outcome Measures:

- Change in cost-effectiveness data [Time Frame: Baseline, immediately after the intervention, and 12-month follow-up]

Cost-effectiveness results will be calculated by the ICER, defined as the difference in mean costs between interventions divided by the difference in their effectiveness according to the symptom questionnaires’ mean scores.

The healthcare data collected will be used for cost calculations. To calculate healthcare-related costs, an ad hoc questionnaire will be used to collect emotional disorder-related healthcare data (public and private healthcare consultations, accidents, medical tests, and sick leaves in the past 3 months; psychotropic drugs or other medication, and their posology).

- Change in cost-utility data [Time Frame: Baseline, immediately after the intervention, and 12-month follow-up]

Cost-utility will be measured through the healthcare data collected above and the European Quality of Life Scale (EuroQoL, EQ) [71], calculating the QALYS and the ICURs, defined as the difference in mean cost divided by the difference in mean QALYs. The Spanish version of the 5-domain, 5-level EuroQol (EQ-5D-5L) [72,73] will be used to assess health status in five dimensions (mobility, self-care, daily activities, pain/unease, and anxiety/depression) with five levels of severity (no problems, slight problems, moderate problems, severe problems, and either extreme problems or unable to perform activity). The scores obtained in the different dimensions can be combined to create a 5-digit code describing the patient's state of health, being able to stablish up to 3125 different combinations, and therefore, different possible health states. This system was converted into a utility score using the value set for Spain from the EQ-5D-5L Crosswalk Index Value downloaded from the EuroQol website (<https://euroqol.org/euroqol/>).

Secondary Outcome Measures:

- Change in depressive symptoms: Patient Health Questionnaire - 9 item (PHQ-9) [Time Frame: Baseline, immediately after the intervention, and 12-month follow-up]

The PHQ-9 [54] is the depression module of the PHQ [74, 75] that scores the 9 DSM-IV depression criteria in the last two weeks. Is a nine item, self-report scale that ranges from 0 to 27 (higher scores means a worse outcome).

- Change in anxiety symptoms: Generalized Anxiety Disorder - 7 item (GAD-7) [Time Frame: Baseline, immediately after the intervention, and 12-month follow-up]

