The GAD-7 [56] assesses common anxiety symptoms in the last two weeks. It is composed of seven self-report items ranging from 0 to 21 points. Higher scores means a greater presence of anxiety symptoms.

- Change in somatic symptoms: Patient Health Questionnaire - 15 item (PHQ-15) [Time Frame: Baseline, immediately after the intervention, and 12-month follow-up]

The PHQ-15 [58] is the somatization module of the PHQ and scores symptoms present in the past four weeks. The scale is composed of fifteen self-report items, ranging from 0 to 30. Higher scores means a worse outcome.

- Change in functioning: Sheehan Disability Scale (SDS) [Time Frame: Baseline, immediately after the intervention, and 12-month follow-up]

The SDS [59] is a five item self-reported scale composed of three main domains (work, family and social functioning) and two optional items (perceived stress and perceived social support). It ranges from 0 to 50, with higher scores indicating a worse outcome.

- Change in treatment satisfaction [Time Frame: Immediately after the intervention and 12-month follow-up]

Posttreatment and 12-month follow-up assessments will also collect an additional question about treatment satisfaction, through a Likert-type question, ranging from 0 to 10.

Other mechanistic outcome measures:

- Change in rumination: Ruminative Responses Scales (brooding subscale) (RRS-B) [Time Frame: Baseline, immediately after the intervention, and 12-month follow-up]

The RRS-B [76] is composed of five self-reported items, ranging from 5 to 20. Higher scores means a worse outcome.

- Change in worry: Penn State Worry Questionnaire – Abbreviated (PSWQ-A) [Time Frame: Baseline, immediately after the intervention, and 12-month follow-up]

The PSWQ-A [62] measures the pathological worry as an uncontrollable and general state. The scale is composed of eight self-reported items, ranging from 5 to 40. Higher scores means a worse outcome.

- Change in attentional and interpretative biases: Inventory of Cognitive Activity in Anxiety Disorders (IACTA) [Time Frame: Baseline, immediately after the intervention, and 12-month follow-up]

The IACTA was originally developed by [name] [63]. It includes subscales that assess distortions according to Eysenck's four-factor theory [77]. The scale is composed of five self-reported items, ranging from 0 to 20. Higher scores means a worse outcome.

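### The only stated efficacy model is a 2x2 ANOVA, but the clinical scales have three visits, so no stated efficacy analysis compares the arms on them at 12 months

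*Protocol*

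**What the plan says.** The Statistical analysis section of the protocol gives a single efficacy model: "In the efficacy analysis, 2x2 (group x treatment) intergroup-intragroup ANOVAs will be carried out on the dependent measures". It applies this to six groups of measures: symptoms, cognitive-emotional factors, dysfunction, quality of life, satisfaction, and service use with drug consumption. It does not name the two occasions that form the second factor, and it does not mention the 12-month visit. The percentages of probable cases are to be calculated "before and after treatment, according to the cut-off points and decision rules for diagnosis".

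The schedule has three occasions. The Abstract says: "Psychological assessments will be carried out at baseline, post-treatment, and 12-months follow-up". Outcome Measures repeats this scale by scale:

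- Symptoms: "Change in depressive symptoms: Patient Health Questionnaire - 9 item (PHQ-9) [Time Frame: Baseline, immediately after the intervention, and 12-month follow-up". GAD-7 and PHQ-15 have the same frame.
- Functioning: "Change in functioning: Sheehan Disability Scale (SDS) [Time Frame: Baseline, immediately after the intervention, and 12-month follow-up".
- Cognitive factors: "Change in rumination: Ruminative Responses Scales (brooding subscale) (RRS-B) [Time Frame: Baseline, immediately after the intervention, and 12-month follow-up". PSWQ-A, IACTA, CERQ, MCQ and CDTE have the same frame.
- Satisfaction is the exception, with two occasions and no baseline: "Change in treatment satisfaction [Time Frame: Immediately after the intervention and 12-month follow-up".

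After stating the cost-effectiveness hypothesis, the Abstract adds: "In addition, these gains will be maintained in the 12-month follow-up". The primary outcomes, the ICER and the ICUR, are set at post-treatment and 12 months, and the ICER takes its effectiveness term from the mean symptom scores.

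**The concern.** A 2x2 mixed ANOVA has two arms and two levels of one within-patient factor, so three visits do not fit it. The protocol states a specific model that conflicts with its own schedule, which is more than a detail left for later. A statistical analysis plan that handled three visits properly would then contradict the protocol.

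At stake is the durability of clinical benefit. On a before/after reading, a symptom benefit that persists to 12 months and one that has gone by then give the same planned efficacy result. A claim that clinical gains last would have to rest on an analysis chosen later, or on a non-significant change within the TD-CBT arm. Neither shows that an advantage over PMR is maintained.

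**Working it through.** **Structural check.** This needs no assumption about effects.

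1. Levels of the within-patient factor in the stated model: 2.
2. Scheduled occasions for PHQ-9, GAD-7, PHQ-15, SDS, RRS-B, PSWQ-A, IACTA, CERQ, MCQ and CDTE: 3, so ten scales do not match the model.
3. Scheduled occasions for satisfaction: 2, but they are post-treatment and 12 months. Its 2x2 can only be post/12 months, while the before/after wording suggests baseline/post for the rest. One stated model would therefore need different occasions for different outcomes, and it names none.
4. With three visits there are 3 possible pairs (baseline/post, baseline/12 months, post/12 months). The protocol does not choose among them.
5. A group-by-visit model on all three visits is 2x3. With 300 complete cases the interaction degrees of freedom go from (2-1)(2-1) = 1 and 300-2 = 298 to (2-1)(3-1) = 2 and 2 x 298 = 596.

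**Which two occasions are meant?** The within-patient factor is called treatment, the case percentages are before and after treatment, and the recruitment section describes a blinded reassessment only in the post-treatment phase. Baseline/post is the natural reading, but it is an inference.

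**Illustration of what a baseline/post 2x2 can see.** The sample size of 300 (150 per arm) is the protocol's. The protocol gives no SD, effect size, correlation, alpha or power, so 300 cannot be reproduced and the rest is assumed: standardised effect 0.4 at post-treatment, equal correlation r between visits, two-sided 5% test, no dropout, no therapy-group clustering.

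For two occasions the 2x2 interaction test is a t test on change scores. In SD units the change has SD sqrt(2(1-r)), so the expected test statistic is d x sqrt(150/2) / sqrt(2(1-r)).

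- r = 0.3: 0.4 x 8.660 / 1.183 = 2.93; power about Phi(2.93 - 1.96) = 83%.
- r = 0.5: 0.4 x 8.660 / 1.000 = 3.46; power about Phi(3.46 - 1.96) = 93%.
- r = 0.7: 0.4 x 8.660 / 0.775 = 4.47; power about Phi(4.47 - 1.96) = 99%.

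The 12-month effect appears nowhere in this formula. Simulation (4,000 trials per scenario) agrees:

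| r | Effect at post | Effect at 12 months | Baseline/post 2x2 rejects | Baseline/12-month contrast rejects |
|---|---|---|---|---|
| 0.3 | 0.4 | 0.4 | 83.0% | 84.3% |
| 0.3 | 0.4 | 0 | 83.4% | 5.0% |
| 0.5 | 0.4 | 0.4 | 93.4% | 93.2% |
| 0.5 | 0.4 | 0.2 | 93.2% | 41.4% |
| 0.5 | 0.4 | 0 | 92.3% | 5.3% |
| 0.5 | 0 | 0.4 | 5.0% | 92.8% |
| 0.7 | 0.4 | 0.4 | 99.3% | 99.5% |
| 0.7 | 0.4 | 0 | 99.5% | 4.3% |

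Both columns use the same change-score test, so the contrast between them reflects only which visit is used.

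**The case against.** The strongest reply is that the 12-month data are used. The ICER and ICUR are primary and are set at 12 months, the ICER denominator is the between-arm difference in symptom means, and the Abstract plans bootstrap uncertainty. The maintenance sentence directly follows the cost-effectiveness hypothesis, so it can be read as a claim about cost-effectiveness, which the 12-month ratios address. All of this stands. A reader might infer from the 2x2 model that the 12-month data go unanalysed, or that maintenance cannot be tested; the protocol does not support either inference. What remains is narrower. A cost difference divided by a symptom difference is not a stated comparison of symptoms at 12 months, and the SDS and the cognitive scales are outside both ratios.

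Second, the occasions are unnamed, so the 2x2 could be run on several pairs of visits, and satisfaction can only be post/12 months. This is also correct. The protocol does not exclude it, but it does not state it either, and it leaves the choice of pair open across many outcomes.

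Third, 12 months is also after treatment, and the percentages with a 50% or one-SD fall carry no time restriction. That is fair, and the case-percentage wording is supporting evidence only.

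Fourth, the simulation builds in its answer, because a baseline/post test never receives the 12-month value. This is true. The simulation shows the consequence of the structure and is not separate evidence.

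Finally, analysis visits are often fixed in a statistical analysis plan. The explicit 2x2 in the protocol would still need correcting to agree with it.

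**Conclusion.** The mismatch is confirmed: two within-patient levels in the only stated efficacy model against three scheduled visits for ten symptom, functioning and cognitive scales. On the before/after reading, no stated efficacy analysis compares the arms on these scales at 12 months. The conclusion stops there, because 12-month symptom means do enter the primary economic analysis.

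The structural finding depends on no numerical assumption. Its consequence depends on the baseline/post reading, which is the natural one but is not stated. The rejection rates rest on assumed effects and correlations and carry no weight beyond illustration.

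Severity is moderate: the affected scales are secondary or mechanistic, and the primary economic outcomes have their 12-month time point defined.

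**What to change.** Replace the 2x2 ANOVA with one repeated-measures (mixed) group-by-visit model per outcome that uses all scheduled visits.

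- Account for baseline where it is measured, either as an outcome occasion in a 2x3 model or as a covariate with post-treatment and 12 months as the outcome occasions. State which.
- For satisfaction, use post-treatment and 12 months with no baseline term.
- Prespecify the TD-CBT minus PMR difference with 95% CI at post-treatment and at 12 months.
- Judge maintenance of clinical gains by the 12-month between-arm difference, shown beside the post-treatment one, and not by a non-significant within-arm change.
- Report the response percentages (50% and one SD) and the probable-case percentages at 12 months as well.
- Say whether the gains in the Abstract's maintenance sentence are cost-effectiveness, clinical outcomes or both.

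The cost is revised wording in the protocol, and in the statistical analysis plan if one exists. All the 12-month values are already scheduled for collection, so no new data are needed.

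### The only efficacy model stated, a 2x2 pre-post ANOVA, holds two of the three scheduled assessments, so no 12-month between-arm analysis is named for the clinical and mechanistic measures

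*Protocol*

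**What the plan says.** The protocol's Statistical analysis section gives the efficacy model in one sentence: "2x2 (group x treatment) intergroup-intragroup ANOVAs will be carried out on the dependent measures". It applies this model to six families of measure: symptoms, cognitive-emotional factors, dysfunction, quality of life, satisfaction, and a sixth headed cost-effectiveness, with attendance and drug use as examples. The same section counts probable cases of mental disorder on either side of treatment. It promises effect sizes with 95% confidence intervals but attaches no visit to them. Twelve months is not mentioned anywhere in the section.

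The Abstract sets three assessments: "Psychological assessments will be carried out at baseline, post-treatment, and 12-months follow-up". Under Outcome Measures, each symptom, functioning and mechanistic measure except alliance carries "Time Frame: Baseline, immediately after the intervention, and 12-month follow-up". Satisfaction carries "Time Frame: Immediately after the intervention and 12-month follow-up", so it has no baseline value.

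The Primary purpose names post-treatment and 12 months. After the main hypothesis, the Abstract adds that "these gains will be maintained in the 12-month follow-up". It also states that uncertainty will be assessed by bootstrap.

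**The concern.** A two-occasion model cannot hold three assessments. If the section is followed as written, the trial collects symptoms, disability, rumination, worry, biases, emotion regulation and metacognitive beliefs at 12 months and has no stated between-arm analysis of them at that visit. An analysis plan that follows the protocol inherits the gap. One that fills it departs from the only efficacy model the protocol states, and the 12-month contrast then looks chosen afterwards.

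Two lesser points follow from the same sentence. The arm-by-occasion interaction in a 2x2 layout compares mean change between arms, which uses the baseline value less efficiently than adjusting for it. And the one model is applied to measures it does not suit: satisfaction, which has no pre-treatment value, and service use and cost, for which the Abstract already gives another method.

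**Working it through.** **Figures in the plan.** The only related figure is the sample size of 300, 150 per arm. It comes without alpha, power, effect size, standard deviation or dropout, so there is nothing to reproduce. The main check is a count of the design.

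**Occasions and cells.**
- Model as stated: 2 arms x 2 occasions = 4 cells; interaction degrees of freedom (2-1)(2-1) = 1.
- Schedule as stated: 2 arms x 3 occasions = 6 cells; interaction degrees of freedom (2-1)(3-1) = 2.
- The model covers 4 of the 6 cells and 2 of the 3 visits.

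**Which visit is left out.** The within-patient factor is called treatment, and the caseness percentages in the same section are pre- and post-treatment. With no mention of 12 months in the section, the natural reading is baseline against post-treatment. The omitted visit is then 12 months.

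**Precision of the contrast.** Assume equal outcome variance s² at both occasions, correlation r between baseline and outcome, and n per arm.
- 2x2 interaction (difference in mean change): variance = (2/n) x 2s²(1-r).
- Baseline-adjusted difference: variance = (2/n) x s²(1-r²).
- Ratio = (1-r²) / [2(1-r)] = (1+r)/2.

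The protocol gives no value of r, so a range is assumed:

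| r (assumed) | 2(1-r) | 1-r² | Ratio | Unadjusted-change sample size equivalent to 300 adjusted |
|---|---|---|---|---|
| 0.3 | 1.40 | 0.91 | 0.65 | 300/0.65 = 462 |
| 0.5 | 1.00 | 0.75 | 0.75 | 300/0.75 = 400 |
| 0.7 | 0.60 | 0.51 | 0.85 | 300/0.85 = 353 |

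Confidence intervals scale with the square root of the ratio: 0.81, 0.87 and 0.92 of the change-score width.

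**Satisfaction.** It has two values, post-treatment and 12 months. A pre-post contrast needs a pre-treatment value, and there is none.

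**The case against.** The strongest reply is that 12 months is not neglected. The primary outcomes are the incremental cost-effectiveness and cost-utility ratios, stated for post-treatment and 12 months. The first takes its effectiveness term from the symptom questionnaires' mean scores, so a 12-month ratio needs a 12-month symptom difference. The sentence on maintained gains directly follows the cost-effectiveness hypothesis and on its face concerns that. This stands, and it confines the gap to the ANOVA-based analysis of secondary and mechanistic measures. It does not close the gap: a difference used inside a ratio is not a named efficacy contrast, and the mechanistic measures do not enter the ratios. A second ANOVA, baseline against 12 months, could be run, but it is not stated.

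It is also fair to say that a change-score contrast is unbiased under randomisation. The precision point is a gain forgone, not an error.

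A reader might infer more than the text supports:
- *That intention-to-treat is broken.* The section says "all individuals who have entered the study will be considered in their corresponding group", and the context is non-compliance, not missing values. A classical repeated-measures ANOVA does drop a patient with a missing occasion unless values are imputed. But the protocol never says complete cases, and the missing-data rule may sit in an analysis plan that is not shown.
- *That 60 to 90 patients would be lost.* This takes an assumed 20-30% of 300. The protocol gives no dropout rate, and if the model omits 12 months, missing that visit removes nobody from it.
- *That the ANOVA cannot be run at all on satisfaction.* It could be run on the two follow-up values; it would just not be the pre-post model described.
- *That one factor is named twice.* The wording refers to between- and within-group comparison, so treatment is the before/after factor. The label is loose but not duplicated.

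**Conclusion.** The point holds within limits. The one efficacy model stated covers two of the three scheduled assessments, and no 12-month between-arm analysis is named for the clinical and mechanistic measures. That rests on the protocol's own text, with one inference: that the two occasions are baseline and post-treatment.

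The precision forgone depends on r and on equal variances at the two occasions. Adjustment would bring the variance to 65-85% of the change-score value for r between 0.3 and 0.7. The misfit for satisfaction is definite but small.

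This should be fixed, but it does not threaten the primary economic analysis: the affected measures are secondary or mechanistic, and the two ratios have their own stated time points and uncertainty method.

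**What to change.** Replace the 2x2 sentence in the Statistical analysis section with the following.

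- For each continuous symptom, functioning and mechanistic measure, and for quality of life, fit one linear mixed model. The responses are the post-treatment and 12-month values; the fixed effects are arm, visit, arm x visit and the baseline value of that measure.
- Use all available follow-up values, with patients in the arm to which they were randomised. A patient with no follow-up value does not contribute to this model, so a sensitivity analysis for such patients is sensible.
- Report the between-arm difference with its 95% CI at each of the two visits.
- Compare satisfaction between arms at its two visits, without a baseline term.
- Take service use and costs out of the ANOVA list and keep them in the bootstrapped economic analysis.

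A 2x3 layout, or a named baseline-to-12-month contrast, would also close the gap in coverage, but would not by itself bring the gain from baseline adjustment. The cost is one paragraph of text and standard software; every value needed is already scheduled for collection.
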